Given the significant potential of fNIRS and ABR in tinnitus research, and the constraints of prior studies, we have developed this randomized controlled experiment (RCT) to investigate the pathological mechanisms of chronic tinnitus using fNIRS and ABR. The objectives of this trial are: (1) To compare the auditory brainstem response parameters and extracerebral oxygen levels of the cerebral cortex between chronic tinnitus patients and healthy subjects, and to compare the correlation of peripheral-central auditory function under different physiological states. (2) To compare the intervention effects of acupuncture versus sham acupuncture on chronic tinnitus patients from clinical manifestations, ABR parameters, and extracerebral oxygen levels of the cerebral cortex, exploring the correlation of acupuncture intervention on chronic tinnitus from the peripheral-central auditory function at three levels: clinical, target organ, and central.

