## Materials and methods

### Study design

Our research is structured as a regulated and randomized trial with assessor blinding. Seventy-two participants who qualify with chronic tinnitus will be allocated in a 1:1 ratio to either the acupuncture group or the sham acupuncture group. Additionally, we will recruit 15 healthy individuals as subjects for data collection to compare the auditory brainstem response parameters and extracerebral oxygen levels of the cerebral cortex between chronic tinnitus patients and healthy subjects, and to observe the correlation of peripheral-central auditory function under different physiological states. Our protocol’s reporting complies with the Standard Protocol Items: Recommendations for Interventional Trials (SPIRIT) criteria. The SPIRIT for the study is shown in Figure 1, and the flowchart is shown in Figures 2, 3.

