### Outcome measures

Clinical Results: Clinical result metrics encompass the Tinnitus Handicap Inventory (THI), ABR testing, and fNIRS data collection. Evaluations will be carried out at baseline, after 10 treatment sessions.

THI score: The THI is a self-reported checklist that’s quick, simple. To manage and interpret, and covers a wide range of issues. It consists of 25 items, each scored from 0 to 4. An elevated THI indicates a more severe level of tinnitus.

ABR testing: The test records the peak latencies (PL), wave amplitudes, and interpeak intervals (IPL) of the subjects at various stimulation rates, as well as the differences in PL and IPL at the two stimulation rates (ΔPL and ΔIPL) to evaluate the function of the peripheral auditory nerve.

fNIRS data acquisition and processing: Cortical blood oxygen data will be collected to evaluate the central function of the subjects.

fNIRS results: fNIRS scans will be conducted at baseline, and after 10 treatment sessions. The blood oxygen concentrations measured include the concentrations of oxygenated hemoglobin (HbO), hemoglobin that has lost oxygen (HHb), and total hemoglobin (THb) in every measured channel.

fNIRS functional connectivity intensity: The intensity of functional connectivity between regions can quantify the relationships between routes or areas of interest within the fNIRS time plots. This is computed using the Pearson correlation coefficient between the average time series of any pair of channels of interest. The functional connectivity strength between channels of interest, as well as between channels of interest and other channels, is computed using NIRSKIT software. This software will help in analyzing the correlation between the time series data from different channels, providing insights into the connectivity patterns within the brain that may be associated with tinnitus and its treatment.

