### Analytical statistics

Date analysis will be done using SPSS version 26 (IBM Corporation, Armonk, NY, 2019), with a two-sided significance threshold established at 0.05. In terms of data description, continuous data is presented as mean ± standard deviation (x ± s), and categorical and ordinal data is stated as proportions (%). The intervention effects will be represented by OR and 95% CI. Data on immediate and cumulative effects of the two acupuncture groups, clinical scoring, ABR parameter analysis, and fNIRS data analysis is compared using T-tests. Permutation tests will be used, and multiple comparisons will be examined using False Discovery Rate (FDR) correction. The differences in THI scores, ABR parameters, and functional values of brain regions will be analyzed for correlation using Pearson’s correlation analysis, with inspection level *α* = 0.05.

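### The planned Pearson correlations have no term for arm; if the randomised arms are pooled, treatment effects on two outcomes alone can create a correlation or hide one

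*Protocol article*

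**What the plan says.** The section Analytical statistics names one method for relating the outcomes to each other: "The differences in THI scores, ABR parameters, and functional values of brain regions will be analyzed for correlation" "using Pearson’s correlation analysis", at level 0.05. The general rule in the same section is a "two-sided significance threshold established at 0.05". It also says that "multiple comparisons will be examined using False Discovery Rate (FDR) correction". No arm term, partial correlation, stratification or within-arm analysis is named for the correlations there or elsewhere in the article.

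The purpose is in the second objective at the end of the Introduction: "exploring the correlation of acupuncture intervention on chronic tinnitus from the peripheral-central auditory function at three levels: clinical, target organ, and central". The three levels correspond to THI, ABR and fNIRS.

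On design, "Seventy-two participants who qualify with chronic tinnitus will be allocated in a 1:1 ratio" to acupuncture or sham (Study design), and "Evaluations will be carried out at baseline, after 10 treatment sessions" (Outcome measures). The Discussion hypothesises that the technique will both relieve tinnitus and bring larger changes in neural activity, although the comparator named there is conventional acupuncture and not sham.

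**The concern.** In a two-arm trial, allocation can be a common cause of the change in two outcomes. If acupuncture lowers THI and also shifts a cortical or ABR measure, patients in one arm tend to have both changes and patients in the other neither. A scatter over both arms then slopes because it joins two clouds, even if neither cloud has a slope of its own. Randomisation does not remove this, because allocation is the source. FDR correction does not remove it either, since it deals with the number of tests and not with what each test measures.

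The trial hopes for treatment effects at more than one level, which is the condition under which this happens. At stake is how the second objective is read: a pooled correlation could be taken as a link between clinical, peripheral and central response when it only restates that treatment moved two things.

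**Working it through.** **Inputs.** 72 patients randomised 1:1, so 36 per arm; 30 per arm evaluable by the article's sample-size section; two-sided α = 0.05. The article states no expected correlation, power or sample size for the correlations, so there is no figure of its own to reproduce here. It also gives no effect sizes for THI, ABR or fNIRS changes. The values of d below are therefore assumptions, shown as a range.

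**Formula.** Let the two changes have SD 1 and correlation ρ within each arm, and let the arms differ by d1 and d2 SD. With 1:1 allocation, pooling adds d1²/4 and d2²/4 to the variances and d1·d2/4 to the covariance:

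pooled r = (ρ + d1·d2/4) / √[(1 + d1²/4)(1 + d2²/4)]

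With ρ = 0 and d1 = d2 = d this becomes (d²/4)/(1 + d²/4):
- d = 0.5: 0.0625/1.0625 = 0.06
- d = 0.8: 0.16/1.16 = 0.14
- d = 1.0: 0.25/1.25 = 0.20

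**Rate of nominally significant results.** This was simulated with normal data, ρ = 0 and 40,000 trials per setting, for a single correlation before any FDR step. Pooled Pearson was tested on N − 2 degrees of freedom and the arm-adjusted partial correlation on N − 3.

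| d1 / d2 | pooled r | pooled, 30 per arm | pooled, 36 per arm |
|---|---|---|---|
| 0.8 / 0 | 0.00 | 5.0% | 4.9% |
| 0.5 / 0.5 | 0.06 | 7.5% | 8.0% |
| 0.8 / 0.5 | 0.09 | 10.5% | 11.8% |
| 0.8 / 0.8 | 0.14 | 18.5% | 21.4% |
| 1.0 / 1.0 | 0.20 | 34.6% | 40.5% |

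The arm-adjusted rate was 4.8–5.1% in every setting run with ρ = 0. A plain Pearson correlation inside the acupuncture arm alone gave 4.9–5.1%.

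**Masking.** With a real within-arm correlation ρ = 0.3 and arm effects of 0.8 and −0.8, pooled r = (0.3 − 0.16)/1.16 = 0.12. At 30 per arm the pooled test rejects in 13.6% of trials. The arm-adjusted test has mean r 0.30 and rejects in 64.6%.

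**The case against.** The strongest reply is that pooling is nowhere stated. If the correlations are run separately in each arm, plain Pearson carries no such bias, as the within-arm simulation shows. The first objective, which compares correlations between physiological states, does call for correlations by group, and the second could be read as concerning the acupuncture arm alone. A journal article may also leave the analysis set to a fuller document. And a pooled correlation is a true feature of the pooled population, so a significant result is not an error in the test's own terms.

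Much of this stands:
- A reader might infer that Pearson's method is itself wrong here because it cannot take a covariate. The documents do not support that: within an arm it is sound. The weakness lies in applying it without arm to pooled patients.
- A reader might take 0.72 as the plan's own effect size, since 30 per group with α 0.05 and 80% power implies a Cohen's h of that size. But h belongs to a comparison of two rates, and the two rates are not given. It says nothing about mean changes in ABR or fNIRS, so it is not used here.
- A reader might infer that the whole mechanistic case rests on these correlations, or that the trial will present them as mechanism. The article speaks of exploring correlation, and it also plans between-arm comparisons of ABR and fNIRS, which this point does not touch.

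What remains is that the article does name a method, and as written nothing in that method separates association among patients treated alike from a shared effect of allocation. If within-arm analysis is intended, saying so takes the same one sentence.

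**Conclusion.** The point holds conditionally and supports a cheap improvement. It rests on two readings that the text suggests but does not state: that the differences are pre-post changes and that the arms are pooled. It also needs a treatment effect on both variables of a pair. The size depends on assumed effects: modest at half an SD on both, and large only from about 0.8 SD on both. These figures assume normal data and no within-arm correlation. The distortion works in either direction, so adjustment protects against a missed association as well as a spurious one.

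Adjustment for arm does not turn the correlation into evidence of mechanism. Both changes are measured after randomisation, so their association within arms remains observational.

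**What to change.** For the randomised patients, replace the plain pooled Pearson correlation in Analytical statistics with a partial correlation, or a regression of one change on the other, adjusted for randomised arm. Show the correlation within each arm beside it, because a common adjusted estimate assumes that the two arms have similar correlations. State that differences means change from baseline to the assessment after treatment, if that is intended. Report the result as an association among patients treated alike.

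The cost is one sentence in the analysis section and one degree of freedom, with no extra patients or measurements. Adjustment for baseline values is optional and not part of the needed change.

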### Sample size estimation

The formula for calculating the two independent sample sizes in Sun Zhenqiu’s “Medical Statistics” is:

$$n=1641.4\times {\left[\frac{\left(u_{a}+u_{\beta }\right)}{\sin^{-1}\sqrt{P_{1}-\sin^{-1}}\sqrt{P_{2}}}\right]}^{2}$$

In the formula, *n* represents the required sample size, the two population rates’ predicted values are, respectively, denoted by P_1_ and P_2_, while u_α_ and u*_β_* are the *u* values according to the exam level *α* and type II error probability *β*, respectively. Assuming *α* = 0.05 and *β* = 0.20, through calculation, the required sample size for each group is 30 cases. Based on a 20% exclusion rate, 36 cases should be included in each group, for a total of 72 patients.

According to the requirements for data analysis in imaging studies, a minimum of 12 healthy subjects should be included. Considering potential uncertainties such as subject head movement during scanning that may render data unusable, to ensure the reliability of data analysis, it is advisable to include 15 healthy subjects.

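### The 30 per group comes from a formula for two unstated rates, but every listed outcome measure is a score or continuous and is compared by t-test, so the implied 80% power is unsupported for any planned analysis

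*Protocol article*

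**What the plan says.** Sample size estimation in the protocol article uses the arcsine formula for two independent proportions. It describes the terms with the words "represents the required sample size, the two population rates". The error rates are given ("Assuming *α* = 0.05 and *β* = 0.20"), and the result follows directly: "through calculation, the required sample size for each group is 30 cases". The enrolment target comes next: "Based on a 20% exclusion rate, 36 cases should be included in each group, for a total of 72 patients". No value for P1 or P2 appears in that section or elsewhere in the article.

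Outcome measures states: "Clinical result metrics encompass the Tinnitus Handicap Inventory (THI), ABR testing, and fNIRS data collection". The THI is a sum of 25 items scored 0 to 4. The ABR variables are latencies, amplitudes and intervals. The fNIRS variables are haemoglobin concentrations and Pearson-based connectivity. No responder cut-off or effective rate is defined.

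Analytical statistics plans that "clinical scoring, ABR parameter analysis, and fNIRS data analysis is compared using T-tests", "with a two-sided significance threshold established at 0.05". It adds permutation tests with FDR correction and Pearson correlations. It also says that intervention effects will be expressed as odds ratios with 95% confidence intervals, without naming a binary outcome to which they would apply.

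**The concern.** A sample size carries its stated power only for the test and the effect it was calculated for. Here the calculation is for a comparison of two rates, while the listed outcome measures are scores or continuous variables to be compared by t-tests. The figure also cannot be checked, because the two inputs that determine it are not printed.

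The practical stake is how the result will be read. If THI does not differ between acupuncture and sham, a reader will want to know what difference the trial could have detected. The article ties its 80% to no THI, ABR or fNIRS difference, so a null result could not be described as adequately powered and negative on the strength of this text.

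**Working it through.** **Inputs.** From Sample size estimation: alpha 0.05, beta 0.20, 30 per group, 20% exclusion, 36 per group, and no P1 or P2. From Analytical statistics: two-sided testing at 0.05 (the sample-size section does not restate sidedness). The article gives no mean difference or SD for any outcome.

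**1. What the formula computes.** The constant is (180/π)²/2 = 1641.40, so the formula works in degrees and returns n per group:

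n = 1641.4 × [(u_α + u_β) / (arcsin√P1 − arcsin√P2)]²

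The radical is misplaced in the printed version. I take that as typesetting and make nothing of it.

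**2. Reproducing 30.** This cannot be done forwards, because P1 and P2 are missing. Backwards, with u_α = 1.96 and u_β = 0.842:

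- required angle = (1.96 + 0.842) × √(1641.4/30) = 20.7 degrees
- as Cohen's h: 2 × 20.72 × π/180 = 0.72

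**3. Which rates fit.** Two-sided n per group for some assumed pairs:

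| P1 vs P2 | n per group |
|---|---|
| 90% vs 60% | 29.8 |
| 80% vs 46% | 30.0 |
| 50% vs 17% | 30.2 |
| 80% vs 50% | 37.9 |
| 90% vs 70% | 59.0 |

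With a one-sided u_α, 80% versus 50% gives 29.9. So 30 is attainable, but the article does not say from which pair, or whether one- or two-sided.

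**4. What the planned t-test delivers.** Two-sided 0.05, two independent groups, noncentral t. The standardised difference d detectable with 80% power is:

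| Evaluable per arm | d |
|---|---|
| 28 | 0.76 |
| 29 | 0.75 |
| 30 | 0.74 |
| 36 | 0.67 |

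The normal approximation at 30 per arm is 2.802 × √(2/30) = 0.72. On the article's own 20% exclusion, 36 × 0.8 = 28.8, so about 29 per arm are evaluable and the relevant figure is about 0.75.

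**5. Power at 30 per arm over an assumed range of true d:**

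| d | Power | n per arm for 80% |
|---|---|---|
| 0.3 | 21% | 176 |
| 0.5 | 48% | 64 |
| 0.7 | 76% | 34 |
| 0.8 | 86% | 26 |
| 1.0 | 97% | 17 |

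**6. In THI points.** The article gives no THI SD. If it were 20 to 25 points (my assumption), then at 29 per arm 0.749 × 20 = 15.0 and 0.749 × 25 = 18.7, so roughly 15 to 19 points.

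**The case against.** The strongest reply is that a binary endpoint was intended. The promised odds ratio with a confidence interval is an effect measure for a binary outcome, and together with a two-rates formula it suggests an effective-rate comparison that the article did not spell out. That may be so. It does not rescue the calculation: no such outcome is defined, no test of two proportions is planned, and an odds ratio does not describe a t-test on scores.

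Second, this is a condensed article. The full protocol may hold P1, P2 and a responder definition. That stands as a limit: one cannot say that no THI difference was ever set, only that none appears here. It does not remove the visible conflict between the printed basis for the sample size and the printed outcomes and tests.

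Third, not everything in the trial is continuous and t-tested. Adverse-event frequency is recorded, and permutation tests and correlations are planned. The point is therefore confined to the measures listed under Outcome measures. The sample size is not linked to safety, and neither of the other methods compares two rates.

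Fourth, a reader might infer that the trial is underpowered. The documents do not support that. If the unstated rates came from dichotomising a normally distributed THI (an assumption), pairs that give about 30 per group correspond to d of about 0.91 to 1.03, and the t-test at 30 per arm would have about 93% to 97% power. With a smaller true effect, power would be much lower. The article does not say which case applies.

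**Conclusion.** The concern holds in this form. The calculation behind "the required sample size for each group is 30 cases" is for two rates that are not given, and it matches neither the listed outcome measures nor the planned t-tests. The implied 80% power is unsupported for any planned analysis; whether it is too high or too low cannot be determined from the article.

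The t-test figures in the working rest on an unadjusted two-sided comparison. The true-difference values and the THI SD are assumptions, because the article supplies neither.

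This should be corrected, because it is the article's only stated rationale for the randomised sample size. It does not show that 72 patients is the wrong number.

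**What to change.** Keep the total at 72. Replace the rates calculation with one for the planned two-sided t-test on a named outcome, such as THI after 10 sessions, and state the assumed SD, its source and the target difference. Then state what the design delivers: with 36 per arm and 20% exclusion (about 29 evaluable), 80% power for a standardised difference of about 0.75, or 0.74 if 30 per arm are evaluable. If the analysis is to adjust for baseline THI, calculate that case separately, because these figures apply to the unadjusted t-test only.

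If a rate was the real basis, define the responder outcome and its cut-off, give P1 and P2, and plan the two-proportion test that goes with the odds ratio.

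The cost is a rewritten paragraph and no extra patients; the second route also adds an endpoint definition and a test. The downside is that the detectable effect, once stated, may look less favourable than an unqualified 80%.

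### The 20% exclusion allowance is computed as 30 × 1.2 = 36 per group; a 20% loss from 36 leaves about 28.8, slightly below the 30 the plan requires (minor)

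*Protocol article*

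**What the plan says.** The Sample size estimation section of the protocol article uses an arcsine formula for comparing two rates, with α = 0.05 and β = 0.20. It reports that "the required sample size for each group is 30 cases". The next sentence makes the allowance for losses: "Based on a 20% exclusion rate, 36 cases should be included in each group, for a total of 72 patients".

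The total of 72, split 1:1, is repeated in the Abstract and under Study design. No section gives the 20% another meaning or names a further reserve. The two rates in the formula are defined only as symbols ("the two population rates’ predicted values are, respectively, denoted by P"), with no numerical values. The test level is two-sided according to Analytical statistics ("with a two-sided significance threshold established at 0.05"); the sample-size section does not state sidedness.

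**The concern.** Three printed figures, 30 required, 20% lost and 36 enrolled, cannot all be true. An exclusion rate ordinarily applies to the patients who enter the trial, so the enrolled number is the required number divided by (1 − rate). The plan multiplied the required number by (1 + rate), which always gives a smaller figure.

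At stake is whether the recruitment target protects the number the plan says it needs. Under the plan's own loss assumption it falls a little short, and a reader who takes the sentence at face value will believe that a 20% loss is fully covered.

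**Working it through.** **Inputs, all from the protocol article**
- Required per group: n₀ = 30 (Sample size estimation)
- Loss rate: d = 0.20 (same section)
- Enrolled: 36 per group, 72 in total (same section; the total also under Study design)
- α = 0.05, taken as two-sided from Analytical statistics; β = 0.20
- The two rates: no values given

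**Step 1. Reproduce the plan's figure.** n₀ × (1 + d) = 30 × 1.20 = 36 per group, and 2 × 36 = 72. This matches exactly.

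**Step 2. Apply the loss to those enrolled.** 36 × (1 − 0.20) = 28.8 per group; 72 × 0.80 = 57.6 in total. The requirement is 30 per group, 60 in total. The shortfall is 30 − 28.8 = 1.2 per group, or 2.4 in total.

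**Step 3. Find the loss that 36 does cover.** (36 − 30)/36 = 6/36 = 16.7%.

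**Step 4. Find the number that covers 20%.** n₀/(1 − d) = 30/0.80 = 37.5, rounded up to 38 per group, 76 in total. That is 2 more per group and 4 more overall (4/72 = 5.6%).

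**Step 5. Could rounding explain 36?** Dividing by 0.80 gives 36 only from a requirement of 36 × 0.80 = 28.8, which would round up to 29 and not to 30. Whole-number requirements of 28 and 29 give 35 and 36.25 (37 after rounding up). So even if the printed 30 was rounded up from just above 29, 36 would still be too few.

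**Step 6. Effect on power.** Under the arcsine formula, if n₀ per group gives exactly 80% power, then n per group gives

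Φ[(1.960 + 0.842) × √(n/n₀) − 1.960].

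The rates cancel, so they are not needed. What is needed is the unrounded n₀, which the article does not print. Assuming that it lies between just above 29 and 30:

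| n per group | Loss from 36 | Power if n₀ = 30 | Power if n₀ is just above 29 |
|---|---|---|---|
| 28.8 | 20% | 78.4% | 79.7% |
| 28 | 8/36 = 22.2% | 77.2% | 78.6% |

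Only the first row matches the plan's 20%. At a one-sided level, the 28.8 figure with n₀ = 30 would be 78.6%, so sidedness hardly matters.

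**The case against.** The strongest defence is that the 20% was meant as a mark-up on the 30 required, in which case 36 is exact. The wording does not support this. The sentence speaks of an exclusion rate and of cases to be included, and exclusions come out of those included. Nothing elsewhere in the article redefines the rate.

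The second defence is about size, and it stands. The gap is about 1.2 patients per group. It biases nothing, changes no analysis and would not alter how a result is read.

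A reader might go further and infer that the trial loses its 80% power in a way that matters, that power falls to about 77%, or that more patients must be recruited. The documents do not support any of these:
- The 77.2% figure needs 28 in both groups, a loss of 22.2%, which is more than the plan assumes. It also takes the unrounded requirement to be exactly 30.
- The 80% is itself nominal. The formula compares two rates, but the sample-size section names no outcome and gives no rates, while Analytical statistics compares clinical scores, ABR and fNIRS data by t-tests. A drop of one or two points in a figure that cannot be reproduced carries little practical weight.
- The inconsistency can be removed by rewording, so it does not compel a larger trial.

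That the 30 cannot be re-derived without the rates is true, but it does not affect this point. The allowance is wrong whatever produced the 30.

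**Conclusion.** Wrong as written, and minor. The 20% was applied to the number required instead of the number enrolled. As a result, 36 per group leaves about 28.8 after a 20% loss instead of the 30 the plan calls for, and it covers at most a 16.7% loss. This conclusion uses only figures printed in the article and takes the 30 as given.

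The power consequence is conditional. If the unrounded requirement lies between just above 29 and 30, and the level is two-sided 0.05, a 20% loss puts power at about 78.4% to 79.7%, that is 0.3 to 1.6 points below the nominal 80%. The sentence should be corrected because it justifies the trial's size and is arithmetically inconsistent, not because the trial is materially weakened.

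**What to change.** Keep 72 patients and correct the one sentence in Sample size estimation, in either of two ways:
- state that 36 per group allows for losses of up to 16.7% (6/36) while retaining 30; or
- keep the 20% and state that it leaves about 28.8 per group (about 57 to 58 in total), with power slightly below the nominal 80%. If a figure is printed, give it as about 78.4% to 79.7% together with the assumption behind it.

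If a 20% loss and 30 remaining per group must both stand, the matching figure is 38 per group, 76 in total, and the total in the Abstract and under Study design must change with it.

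Either rewording costs one sentence and a slightly less favourable claim. The third course costs four more patients.
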